### Primary outcome measure

Our primary outcome measure is a change in the patient’s QoL at 2 months, determined by the Logsdon QoL-AD scale, assessed by the primary caregiver [28]. We chose the patient’s QoL criterion because it is a multidimensional criterion that can be assessed by validated tool. We chose the Logsdon QoL-AD scale because it has been validated in our population [29]. This scale can be completed by the patient or the caregiver.

Considering that self-report could be difficult for mild to moderately severe AD patients, we chose to use hetero-evaluation by the caregiver as primary outcome, as in many clinical trials involving AD dyads and targeting the patient’s well-being [30]. The caregivers are instructed to carry out the rating of the QoL according to the instructions for interviewers provided by Logsdon and colleagues [28]. They are asked to fill in the scale as a self-administered 13-item questionnaire, concerning their relative’s QoL. We tried to minimise the risk of an experimenter’s bias by using a method of collection of data that does not require active involvement of an interviewer.

Nevertheless, we are collecting the self-assessed Logsdon QoL-AD as a secondary outcome.

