**Methods:**

The THERAD study (THerapeutic Education in Alzheimer’s Disease) is a 12-month randomised controlled trial that started in January 2013. This paper describes the study protocol. THERAD plans to enroll 170 dyads (AD patient and caregiver) on the basis of the following criteria: patient at a mild to moderately severe stage of AD, living at home, receiving support from a family caregiver. The main outcome is the patient’s quality of life assessed by the Logsdon QoL-AD scale at 2 months, reported by the caregiver. The study is being led by geriatricians trained in therapeutic education at Toulouse University Hospital in France. To date, 107 caregiver/patient dyads have been recruited.

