### Sample size

We hypothesise a similar QoL score in the two groups at baseline, 25 ± 5.5 points (Logsdon Quality of Life in Alzheimer’s disease (QoL-AD) scale including 52 points [28]). To detect an increase of 5% in the total score and a relative variation of more than 10% of the baseline score between trial arms, with an alpha risk of 5% and a beta risk of 20%, and anticipating 20% attrition, 85 dyads are required per group. The total sample size required for the study is 170 dyads (85 per arm).

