### Analysis

Data are collected in the Access database and SAS software (developped by the SAS institute based in Cary, North Carolina, USA) will be used to perform the statistical analysis. Intention-to-treat analysis using a linear mixed model will be performed, adjusting for patient (disease severity) and caregiver (burden) characteristics and occurrence of life events that may interfere with the patient’s QoL. Attrition of dyads has been taken into account. At the moment, at the 12-month visit, there is less than 5% attrition. Moreover, the total sample size required for the study was calculated anticipating a risk of 20% attrition to take into account this phenomenon, which is particularly important in our population [45].

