The THERAD study follows a feasibility study we conducted at Toulouse University Hospital between January 2010 and January 2011. This was a 12-month monocentric quasi-experimental before and after study. The inclusion criteria were the same as those of the THERAD study. The main outcome was the patient’s QoL as assessed by the caregiver. Our secondary outcomes were: patient’s functional autonomy assessed by the Activities of Daily Living and the caregiver’s burden assessed by the Zarit Burden Interview. Twenty-nine dyads of AD patient/caregiver were included. At 2 months there was a significant increase in the patient’s QoL (24.6 ± 5.1 at M0 vs. 27.2 ± 6.0 at M2, *P* = 0.038). This was an encouraging result and the first step in the development of the THERAD study. Of course, this study had limitations, mainly its lack of statistical power. Use of the caregiver’s rating of the AD patients QoL can also be considered a limitation, in a combined intervention programme, but this limitation appears to be minimal. Indeed the educational programme was not specifically designed to improve the caregivers’ burden or depression, factors that have been pointed out to influence caregiver’s perception of the patient’s QoL. However, acknowledging this problem of proxy rating, we chose to add self-rating methods as a secondary outcome in the THERAD study. Moreover, it has been demonstrated that self-rating and caregiver’s ratings are complementary and should be treated separately [20]. This improvement in patients’ QoL was in accordance with the evidence from the literature. As mentioned earlier, a systematic review has shown that multidimensional approaches including, but not involving only, therapeutic education, caregiver support and respite improve the patient’s QoL [23]. In addition, it has been shown that therapeutic educational programmes can improve patients’ QoL in many chronic diseases [61],[62].

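### The primary outcome is worded as a change in QoL-AD but sized with the baseline SD, and baseline QoL-AD is not among the named covariates; a baseline-adjusted estimate would be more precise at no cost

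*Protocol article*

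**What the plan says.** Under Primary outcome measure, the protocol article states: "Our primary outcome measure is a change in the patient’s QoL at 2 months", rated by the caregiver. The abstract words it without the element of change: "The main outcome is the patient’s quality of life assessed by the Logsdon QoL-AD scale at 2 months, reported by the caregiver".

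Under Sample size, the planning values are cross-sectional: "We hypothesise a similar QoL score in the two groups at baseline, 25 ± 5.5 points". The target is "To detect an increase of 5% in the total score and a relative variation of more than 10% of the baseline score between trial arms", on a "scale including 52 points". Alpha is 5%, beta is 20%, anticipated attrition is 20%, and the result is 85 dyads per arm. Neither an SD of change nor a correlation between visits is given.

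Under Analysis, an intention-to-treat linear mixed model is planned, "adjusting for patient (disease severity) and caregiver (burden) characteristics" and for life events. Baseline QoL-AD is not in that list, although the Detailed study scheme has the caregiver rate it at the baseline visit (M0), before allocation.

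The Discussion reports a before-and-after feasibility study with the same inclusion criteria in 29 dyads: "At 2 months there was a significant increase in the patient’s QoL", from 24.6 ± 5.1 at M0 to 27.2 ± 6.0 at 2 months (M2), P = 0.038.

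**The concern.** The stated endpoint, the SD used for sizing and the named covariates do not fit together. A change from baseline has its own SD, which depends on how strongly M0 and M2 scores are correlated. With equal SDs at both visits it equals the cross-sectional SD only at r = 0.5. Below that, a change score is noisier than the M2 score alone.

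Baseline QoL-AD is measured on the same scale by the same rater, so it is an obvious covariate for precision. If the primary contrast is a raw M2 minus M0 difference, or an arm-by-visit contrast with separate baseline means per arm (essentially the same comparison), precision that the data already contain is lost. At stake is the precision of the primary result, and whether the power statement describes the analysis that will be done.

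**Working it through.** **Inputs.** From Sample size: SD 5.5, 85 per arm, alpha 5% (taken as two-sided), power 80%, attrition 20%, difference δ = 5% of 52 = 2.6 points (10.4% of 25). From the Discussion: n = 29, SDs 5.1 and 6.0, mean change 27.2 − 24.6 = 2.6, P = 0.038. From Analysis: attrition so far under 5%. Powers below use the normal approximation.

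**1. The plan's own figure.** n = 2(1.96 + 0.842)² × 5.5² / 2.6² = 70.2 per arm. Multiplied by 1.2 this is 84.3, so 85. The stated size is therefore reproduced by an unadjusted comparison of two means with the baseline SD. After 20% loss, 85 × 0.8 = 68 remain, and power is Φ(2.6 / (5.5√(2/68)) − 1.96) = 78.7%.

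**2. What the baseline SD implies for change.** With equal SDs, SD of change = SD√(2(1 − r)). This equals 5.5 only at r = 0.5.

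**3. What the feasibility study suggests.** Assume a paired t-test on all 29 dyads.
- t with 28 df for P = 0.038 is 2.178.
- SD of change = 2.6 × √29 / 2.178 = 6.43; 95% CI 5.1 to 8.7 (chi-square, 28 df).
- r = (5.1² + 6.0² − 6.43²) / (2 × 5.1 × 6.0) = 0.34; 95% CI −0.03 to 0.63.
- An unpaired test on the same figures gives P = 0.081, not 0.038, which supports the paired reading.
- If only 25 dyads were analysed at M2, the SD of change is 5.92 and r is 0.44. If only 23, they are 5.65 and 0.49.

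**4. Power for δ = 2.6.** The baseline-adjusted residual SD is SD√(1 − r²), which is 5.65 from the M2 SD of 6.0, or 5.18 from the planning SD of 5.5.

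| Analysis | SD | 68 per arm | 81 per arm (about 5% loss) |
|---|---|---|---|
| As planned | 5.5 | 78.7% | 85.3% |
| Raw change, pilot | 6.43 | 65.5% | 73.0% |
| Raw change, lower CI limit of SD | 5.10 | 84.4% | 90.0% |
| Raw change, upper CI limit of SD | 8.69 | 41.4% | 47.7% |
| Baseline-adjusted, M2 SD 6.0 | 5.65 | 76.6% | 83.4% |
| Baseline-adjusted, SD 5.5 | 5.18 | 83.4% | 89.2% |

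The two adjusted rows differ only in the SD assumed. They do not carry the sampling uncertainty in r.

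**5. The comparison without the pilot.** With SD 5.5 at both visits and 68 per arm:

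| r | Raw change | Baseline-adjusted | Variance ratio 2/(1 + r) |
|---|---|---|---|
| 0.3 | 64.4% | 82.4% | 1.54 |
| 0.5 | 78.7% | 88.9% | 1.33 |
| 0.7 | 94.5% | 97.1% | 1.18 |

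At r = 0.34 the ratio is 2/1.34 = 1.49. With the pilot's unequal SDs it is (6.43/5.65)² = 1.30. Adjustment is ahead at every r below 1.

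**The case against.** The strongest reply is that the article does not commit to a raw change analysis. A linear mixed model can carry the M0 score as a response, and with a common baseline mean it behaves much like baseline adjustment. That choice is commonly left to an analysis plan, which is not shown. The abstract's wording also allows a comparison of M2 scores, for which 5.5 is a natural SD and, with baseline adjustment, a conservative one. This stands to the extent that the article cannot be said to leave baseline QoL-AD unused. But it does state an endpoint, a sizing SD and a covariate list, and read together these point to a less efficient estimate than the data allow.

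A reader might infer that power is only about 65% and that the stated 80% is missed. The documents do not support that. The figure rests on one P value from an unnamed test, in 29 dyads who were all treated, carried over to untreated controls. Its interval for the SD includes 5.5. It is for an unadjusted contrast, whereas severity and burden may absorb some variance (how much is unknown). It also assumes 20% loss, against under 5% reported so far. Part of the gap to 80% at 68 per arm comes from the attrition step, since even SD 5.5 gives 78.7% there.

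A reader might also see chance baseline imbalance as a further threat, because randomisation is unstratified. Its standard error is 5.5√(2/85) = 0.84, so ±1.65 points is within the 95% range. On the pilot figures the slope of M2 on M0 is 0.34 × 6.0/5.1 = 0.40, so about 0.60 × 1.65 = 1.0 point would pass into a change contrast. That variation is already in the standard error of the change score, so it is not an additional harm.

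**Conclusion.** The point holds as one of efficiency and consistency. The outcome is worded as a change in one place and as a 2-month score in another, the sizing SD fits a change only at r of about 0.5, and the named covariates omit baseline QoL-AD. A raw change contrast, or an unconstrained arm-by-visit contrast, has about 1.2 to 1.5 times the variance of a baseline-adjusted one for r from 0.7 to 0.34, assuming equal SDs. That advantage does not depend on the pilot.

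The size of any power shortfall does depend on the pilot and is uncertain. Whether the stated 80% is missed is open.

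**What to change.** Define the primary estimate as the between-arm difference in caregiver-rated QoL-AD at M2, adjusted for its M0 value, and use the same wording in the abstract and the outcome section. Either enter M0 QoL-AD as a covariate in the mixed model of the M2, M6 and M12 scores, or fit a constrained longitudinal model with a common baseline mean.

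Restate the power with the SD and correlation that match this analysis, as a range over plausible r and attrition. If the feasibility data are at hand, take the SD of change and r from them directly instead of from the P value.

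The cost is analysis wording only. The M0 score is already collected, and at the time of writing 107 of 170 dyads had been enrolled, so the change can be made before the final analysis.

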### Secondary outcome measure

The secondary endpoints are: the frequency and severity of the patient’s behavioural and psychological symptoms of dementia assessed by the NeuroPsychiatric Inventory [31]; the patient’s functional autonomy assessed by the Activities of Daily Living scale [32] and the Instrumental Activities of Daily Living scale [33]; the patient’s QoL assessed by the Logsdon QoL-AD scale, self-reported; the primary caregiver’s burden assessed by the Zarit Burden Inventory [34]; the primary caregiver’s QoL assessed by the Nottingham Health Profile [35]; and the primary caregiver’s mood assessed by the mini-Geriatric Depression Scale [36].

We are collecting these data at 2 months, 6 months and 12 months. Lastly, we are collecting information on factors that can influence QoL, as demonstrated in the literature, such as acute disease for both the patient and his/her primary caregiver, change in home care support, hospitalisation or institutionalisation [37].

### Detailed study scheme

The entry and follow-up procedures are illustrated in Figure 1.

All visits are being performed by geriatricians who are hospital practitioners trained in therapeutic education. Written agreement to participate is being obtained from all participants (patients and caregivers).

The baseline visit (M0) concerns both the patient and the caregiver. In both the intervention group (group A) and the control group (group B), the patient receives a consultation led by a geriatrician. This includes a clinical examination and comprehensive geriatric assessment (Mini-Mental Score Examination, weight, one-leg balance, sensorial impairment, co-morbidities, pharmacological and nonpharmacological therapies) [38]. The outcomes concerning the patient are assessed at baseline by: Logsdon QoL-AD reported by the primary caregiver and patient; and the Activities of Daily Living, the Instrumental Activities of Daily Living and the NeuroPsychiatric Inventory reported by the caregiver. The secondary outcomes concerning the caregiver are assessed by the mini-Geriatric Depression Scale, the Zarit Burden Interview and the Nottingham Health Profile, self-reported.

At the end of the baseline visit, each patient/caregiver dyad is randomly allocated to group A or group B (Figure 1). The random number is generated by a computerised generator using block randomisation. The block size is concealed from all researchers. As described in the intervention section and in Figure 1, at the end of the baseline visit the dyads of the intervention group (group A) receive the first step of the intervention: the educational diagnosis (cf. Intervention).

The second 2-month visit (M2) also involves the dyads of both groups A and B, but the first part differs between groups. As described in Intervention, at the beginning of M2 the participants in the intervention group (group A) benefit from the last part of the intervention and its assessment. The participants of both groups then receive a clinical examination, comprehensive geriatric assessment and assessment of endpoints.

Participants in groups A and B receive a follow-up visit at 6 months and at 12 months, including the assessment of the primary and secondary endpoints.

### Intervention

The intervention consists of a therapeutic educational programme. The total duration of intervention is 2 months. The intervention is composed of two individual sessions (M0 and M2) (for both patients and caregivers) and four group sessions (for caregivers only) between M0 and M2.

The first individual session – the educational diagnosis – takes place at the end of M0. Indeed, the educational diagnosis is the first step of any educational process [39],[40]. Via this specific stage, the educational team can better understand the different aspects of the patient’s personality and life history, and those of the caregiver as well. This stage allows the team to identify their needs, assess their potential and consider their requests. Its major purpose is to help the dyad to formulate a project by identifying skills to acquire or strengthen and defining realistic goals to reach [40]. The patient participates in this individual session because it is important to collect their representations and beliefs about the disease, which are useful for the educational process of the dyad. As a matter of fact, many people with dementia do not have the opportunity to raise their concerns once a diagnosis is made, and often feel isolated [41]. The AD patient’s educational diagnosis is supported by a specific tool, developed by the French Ministry of Health [42]. This tool is a booklet specifically designed for patients. It is performed as a semi-directive interview with patient-centred communication techniques, and educational techniques. The patient can also note his/her thoughts about daily life in the booklet. This educational diagnosis is then linked with that of the caregiver so that the team can establish a semi-tailored plan with learning priorities for the caregiver depending on the patient’s educational diagnosis (for example, to adapt his/her communication style in stressful situations). The intervention is supported by the use of a monitoring scheme established at this step, used during the follow-up sessions. Indeed, therapeutic patient education is a continuing process adjusted to disease course and patient lifestyle. A formal document is delivered to patients, called the ‘Alzheimer’s Card’, also developed by the French Ministry of Health [43]. This card is kept by the patient. It includes information on disease management (for example, name of the family practitioner, drugs taken, telephone number of the relatives) and provides counselling in legible and understandable form for cognitively impaired subjects.

Then caregivers benefit from four group sessions, one per week for a month. These sessions are conducted in small groups (six to eight caregivers) and last 3 hours each. They aim towards allowing people to gain better understanding of their relative’s illness, have their concerns addressed and have their feelings expressed. We have planned four group sessions for caregivers, each focusing on a specific aspect of the disease: Session 1 (S1) – knowledge of the disease, understanding of the symptoms, functional abilities; Session 2 (S2) – treatment (pharmacological and nonpharmacological aspects), behavioural and psychological symptoms of dementia in daily living; Session 3 (S3) – management of crisis situations and prevention of caregiver’s exhaustion; and Session 4 (S4) – assistive devices, home care support and care pathways. Table 1 describes the objectives and topics of the group sessions.

**Table 1 T1:** Educational objectives of the group sessions in the intervention group of the THERAD study

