## Methods

### Study design

The THERAD study is a monocentric, randomised, single-blind, controlled trial and has been registered on clinicaltrials.gov since 19 February 2013 [ClinicalTrials.gov: NCT01796314]. The AD patient/caregiver dyads in the intervention group receive a therapeutic educational programme and the dyads in the control group benefit from usual care. The THERAD study will enrol 170 dyads, 85 in the intervention group and 85 in the control group. The entry and follow-up procedures are illustrated in Figure 1. The study protocol was approved by the French Ministry of Health. Informed consent was obtained from all enrolled participants. The Toulouse University Hospital has delivered ethical approval. Blinding of raters is performed in a single-blind experimental design: participants know the full facts (group session), but not the experimenters. The randomisation was done with STATA® Version 11.0. We performed a blocked randomisation. We used a block of four, of fixed size, without stratification. The allocation procedure was conducted by the Department of Epidemiology of the Toulouse University Hospital in Toulouse, France. The randomisation list is printed and kept in this department, protected by a password. At enrolment, a fax is sent by the THERAD study group to this department, together with the participant code and information regarding assignment. The investigators are unaware of the randomisation list. The assignment is concealed for the raters at follow-up visits.

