	**Objectives**
Session 1 (S1): knowledge of the disease	- To identify the cognitive impairment of the patient in everyday life
	- To recognise the remaining functional abilities
	- To determine the nonpharmacological measures to be implemented
Session 2 (S2): pharmacological and nonpharmacological treatments. Behavioural and psychological symptoms of dementia	- To understand the potential effect of pharmacological therapies
	- To identify behavioural and psychological symptoms of the disease
	- To implement nonpharmacological measures to prevent these symptoms
Session 3 (S3): crisis situations. Prevention of caregiver’s exhaustion	- To identify conditions of high risk (treatment modification, concomitant illness, change of environment, relocation)
	- To recognise and prevent caregiver’s burnout
	- To identify their resources
Session 4 (S4): assistive devices and care pathways	- To understand assistive devices, respite and legal aspects raised by the disease
	- To identify the resources available in crisis or emergency situations (general practitioner, specialist consultation, hospitalisation)

THERAD, Therapeutic Education in Alzheimer’s Disease.

Each session is adaptable to the objectives of the participants in each group. The goal we intend to achieve during these group sessions is to develop the caregivers’ coping strategies. It is also part of the educational process to offer them emotional support.

The sessions are led by a geriatrician (S1 and S2) and a nurse (S2, S3 and S4), both trained in therapeutic education, in tandem with stakeholders belonging to the geriatric department: a pharmacist (S2), a psychologist (S3) and a social worker (S4). The pedagogic methods and tools are those currently used in therapeutic educational programmes [40]. We use tools such as storytelling or drawings that allow us to explore the subject’s representations and worries [44]. We also use computer-based activities and brainstorming, as commonly used in health education.

Patients can also receive written documents, when needed, to support the educative process delivered to their relatives during group sessions.

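### Intervention caregivers, who rate the primary outcome, are taught in groups of six to eight, but the sample size assumes independence and the stated model names no session-group effect

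*Protocol article*

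**What the plan says.** The Protocol article randomises individual dyads 1:1 (Methods, Detailed study scheme; Study design): "The THERAD study will enrol 170 dyads, 85 in the intervention group and 85 in the control group". Control dyads receive usual care, and no grouping is described for them.

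In the intervention arm, caregivers attend four weekly group sessions (Methods, Intervention): "These sessions are conducted in small groups (six to eight caregivers) and last 3 hours each". The text under Table 1 adds: "Each session is adaptable to the objectives of the participants in each group". Each dyad also has two individual sessions.

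The primary outcome is the change at 2 months in the patient's QoL-AD score, which the caregiver completes as a self-administered questionnaire (Primary outcome measure).

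The Sample size section starts from "We hypothesise a similar QoL score in the two groups at baseline, 25 ± 5.5 points", states the target as "To detect an increase of 5% in the total score and a relative variation of more than 10% of the baseline score between trial arms", and concludes: "with an alpha risk of 5% and a beta risk of 20%, and anticipating 20% attrition, 85 dyads are required per group". It mentions no intra-group correlation or design effect.

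The Analysis section says: "Intention-to-treat analysis using a linear mixed model will be performed". It then names the adjustment for disease severity, caregiver burden and life events. It names no random effect of any kind.

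**The concern.** This is a partially nested design: one arm contains about 11 to 14 treatment groups (85/8 to 85/6) and the other contains unconnected dyads. Caregivers who spend four 3-hour sessions together may come to share coping strategies, or a standard for judging their relative's quality of life. The person grouped is also the rater, so a shared shift in rating standard would reach the primary outcome directly. Content that can be adapted to each group gives a further route.

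Any such shared component adds between-group variance to the intervention mean, and an analysis treating all dyads as independent would leave it out. The confidence interval would be too narrow, a false-positive claim somewhat more likely, and the planned power optimistic. The adjustment terms that the article names would not absorb this variance. Nor would a random effect for the dyad, if one were used for the repeated visits.

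**Working it through.** **Inputs from the article.** SD 5.5; difference 5% of 52 = 2.6 points; alpha 5% (taken as two-sided, which reproduces the stated figure); power 80%; attrition 20%; 85 per arm; group size m = 6 to 8.

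**Assumed.** The article gives no ICC, so the range is 0.01 to 0.10. Total variance is taken as equal in the two arms.

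**1. The stated sample size.** n = 2 × [5.5 × (1.960 + 0.842)/2.6]² = 70.25 per arm. Then 70.25 × 1.2 = 84.3, rounded up to 85. The figure is reached with no design effect. (Dividing by 0.8 instead would give 88 to 89; that is a separate matter.)

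**2. Formulas.**
- Design effect, intervention arm only: DE = 1 + (m − 1) × ICC.
- True over naive standard error, equal arms: R = √((1 + DE)/2).
- Type I error if group is ignored: 2 × [1 − Φ(1.96/R)].
- Power with a correct standard error: Φ(2.6/SE − 1.96), where SE = 5.5 × √((1 + DE)/n). This normal approximation ignores the lost degrees of freedom.

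**3. One case in full: m = 7, ICC 0.05, n = 68 (85 less 20%).** DE = 1 + 6 × 0.05 = 1.30. R = √(2.30/2) = 1.072. Type I error = 2 × [1 − Φ(1.828)] = 6.8%. SE = 5.5 × √(2.30/68) = 1.011, so power = Φ(2.570 − 1.960) = 73%. Without clustering, SE = 5.5 × √(2/68) = 0.943 and power is 79%.

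**4. Range for m = 6 to 8.**

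| ICC | DE | R | Type I error | Power, 68 per arm | Power, 85 per arm | Enrolled per arm needed (× 1.2) |
|---|---|---|---|---|---|---|
| 0 | 1 | 1 | 5.0% | 79% | 87% | 85 |
| 0.01 | 1.05–1.07 | 1.01–1.02 | 5.3–5.4% | 77–78% | 86% | 88 |
| 0.02 | 1.10–1.14 | 1.02–1.03 | 5.6–5.8% | 76–77% | 85% | 89–92 |
| 0.05 | 1.25–1.35 | 1.06–1.08 | 6.5–7.1% | 72–74% | 81–83% | 96–100 |
| 0.10 | 1.50–1.70 | 1.12–1.16 | 8.0–9.2% | 66–69% | 76–79% | 106–114 |

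A simulated t-test with groups of 7 and 68 or 85 per arm (40,000 runs each) gave 5.0–5.1%, 5.1–5.3%, 5.6–5.8%, 6.6–6.7% and 8.3–8.7% for ICC 0, 0.01, 0.02, 0.05 and 0.10. This agrees with the formula.

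**5. Attrition.** If 20% are lost, groups shrink as well: 7 × 0.8 = 5.6 evaluable members. At 68 per arm this gives DE 1.23, type I error 6.3% and power 74% at ICC 0.05, and 1.46, 7.7% and 70% at ICC 0.10. If 5% are lost (about 81 per arm), power at ICC 0.05 is 79–81% for m = 6 to 8.

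**The case against.** A reader might infer that the planned model leaves session group out, so that the standard error is certainly too small and the trial's type I error exceeds 5%. The article does not support that, for three reasons.

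- It states no random-effects structure. That detail commonly sits in an analysis plan, which is not shown here. The article neither includes nor excludes a group term.
- It gives no ICC. At 0.01 to 0.02 the excess is below one percentage point. Because dyads are randomised individually, a programme that changed no rating at all would create no shared session effect, and type I error would stay near 5%. The excess arises when the average effect is zero but groups differ.
- Several features point to a small ICC: a single centre, the same topics and objectives for every group in Table 1, two individual sessions per dyad, and a questionnaire that each caregiver fills in about their own relative. Sessions are described as adaptable, not as necessarily different, and the article does not say that membership stays fixed over the four sessions.

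The power loss may also never appear. The Analysis section reports under 5% attrition at the 12-month visit so far, and the primary endpoint is at 2 months.

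All of this limits the size and certainty of the point. It does not remove the grouping or change the sample size calculation, which is fully stated and makes no allowance for it.

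**Conclusion.** The point holds conditionally. What the article establishes is one-arm grouping of the people who rate the primary outcome, a sample size that its own inputs reproduce with no design effect, and an analysis description that mentions no session group.

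The inferential consequence needs two further conditions: an ICC above zero, and an analysis that leaves group out. If both hold, the naive standard error is too small by a factor of about 1.01 to 1.16 over the assumed ICC range. At ICC 0.10 this is a material error; at 0.01 it is negligible.

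The effect on power depends mainly on attrition. At the planned 20% loss, power is just under 80% even without clustering, and an ICC of 0.05 costs roughly a further 5 to 7 percentage points. At the attrition reported so far, the spare dyads absorb about that much. They would not correct an understated standard error, which is why the analysis matters more than the sample size. This is an inexpensive improvement to the primary inference, not a defect that invalidates the design.

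**What to change.** 1. Record the session group assigned to each intervention dyad, and keep the assigned group in the analysis even if the caregiver does not attend. If membership can change between sessions, define in advance which group counts.
2. Before results are seen, prespecify in the primary model a random session-group effect that applies in the intervention arm only, with control dyads as singletons. Use small-sample degrees of freedom (Kenward-Roger or Satterthwaite), since there are only about 11 to 14 groups. If the analysis plan already contains this, a sentence saying so is enough.
3. Restate the power for 2.6 points over an assumed ICC range, for example 0.01 to 0.10, at both the planned and the observed attrition. Enrolling more dyads is not proposed.

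The cost is one recorded variable and one extra model term in SAS. The price is a slightly wider interval and fewer degrees of freedom. If the ICC proves to be near zero, little is lost.
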